#### Definition of a serious adverse event

Any adverse event, as defined, that results in hospitalisation or prolonged hospital stay, permanent or prolonged incapacity, significant disruption to daily life, threat to life, death, or any congenital abnormality arising from treatment, will be deemed a serious adverse event.

#### Anticipated adverse events

The procedures involved in this trial are typically safe and well tolerated. Though any serious adverse event is unlikely, there are known potential adverse events with both treatments. These include the following:PainBleedingInfectionPhlebitisStaining of skinPalpable subcutaneous lumpsNew ulcerationDeep vein thrombosisPulmonary embolism, including life-threatening or fatal embolismStrokeNerve injury leading to pain/paraesthesia/reduced sensationSkin breakdown or hypersensitivity reaction secondary to compression/dressingsAdverse or hypersensitivity reaction to local anaesthetic or Sotradecol

#### Adverse event reporting

The principal investigator should be notified of all adverse events. In the event of multiple similar adverse events, or any serious adverse event, the trial monitoring committee and local ethics committee will be notified, and risk analysis is performed.

### Trial treatment

Patients enrolling in the trial will treated with either TIRS or AA according to their randomly assigned group and will then be placed in compression. Compression will take the form of two- or four-layer compression bandaging, using either Profore™ (Smith & Nephew, London, UK) or Coban™ (3M, Maplewood, MN, USA).

### Trial monitoring

The principal investigator will take responsibility for the day-to-day management of the trial supervised by the supervising investigator. Meetings will be held every 2 weeks between the principal investigator and supervising investigator to monitor recruitment, data collection and problems as they arise. The trial monitoring committee will meet as necessary to review safety issues. An independent data monitoring committee has not been established as the trial interventions are low-risk and consist of already-available and recognised treatment strategies. Any safety or equipoise concerns will be reported to those members of the Department of Vascular Surgery in University Hospital Galway who are not involved in the conduct of the trial for their consideration. This will include the results of the interim analysis.

### Personnel

The principal investigator will manage this trial, along with the help from the on-site tissue viability nurse and the co-authors. The principal investigator will specifically have the responsibility for screening and enrolment of patients, data collection at randomisation and follow-up, and statistical analysis.

The trial nurse(s) will assess all wounds prior to allocation and perform blinded assessment at each subsequent follow-up visit.

### Method of blinding

The trial will be assessor blinded. The trial nurse(s) will assess all wounds prior to randomisation and will be blinded to treatment allocation throughout, performing assessments at each follow-up visit. Patients will be instructed not to reveal the nature of their treatment in follow-up. The operation note from the intervention will be filed in the patient notes to allow intentional or emergency access. All members of the trial team involved in data collection and analysis will not be present when the envelope is opened at the time of treatment.

Any treatment decisions required beyond the trial protocol will be made by a member of the surgical team who is already unblinded.

Ultrasound assessment of treated veins will be avoided unless otherwise indicated, to minimise risk of inadvertent unblinding of assessors.

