#### Implementation

On enrolment the principal investigator will assign a trial number to the patient and be informed of the ulcer’s size. An envelope will then be taken from the appropriate stratum. The trial number will be written on the envelope, and the envelope passed to the surgical team. The team performing the procedure will sign the envelope sealed, and open it in the operating room immediately before the procedure. A member of the surgical team will then take appropriate consent from the patient for the specific procedure being carried out.

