#### AA

I.Ultrasound guided micropuncture of the desired axial veinII.Placement of a 5 French-gauge sheathIII.Passage of the Clarivein™ device to the proximal end of the treatment areaIV.Activation of the device, followed by withdrawal at a rate of 1 mm/s, while simultaneously infusing Sotradecol.

Variations of these treatments are at the discretion of the treating surgeon as long as the above steps are met. After treatment, all patients will be placed in compression bandages. They will then be followed up monthly at the same site with changes of their compression bandages in between by their local public health nurse (PHN) weekly, or more frequently as needed. If at any follow-up visit, their ulcer is seen to have healed, the time at which it healed will be noted in weeks from intervention. At this point, they will have completed their follow-up and will exit the trial. Patients in whom the ulcer has not fully healed at 24 weeks will also exit the trial. In either case subsequent treatment will be at the discretion of the surgical team.

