#### First clinic visit

At their 1st visit to the clinic, patients will be screened, and if found to be eligible, the principal investigator or another designated trial investigator will discuss enrolment. If willing, patients will have their baseline data and wound assessment recorded as above and be randomised and treated on the same day as screening unless they wish to defer enrolment.

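### The nurse who judges healing is to stay blinded, but the operation note goes into the patient notes with no stated barrier between the two: an unguarded risk to the primary outcome

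*Protocol article*

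**What the plan says.** The protocol article gives the assessor's role in two places. Under Personnel: "The trial nurse(s) will assess all wounds prior to allocation and perform blinded assessment at each subsequent follow-up visit". Under Method of blinding, the trial nurses "will be blinded to treatment allocation throughout, performing assessments at each follow-up visit".

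The same Method of blinding section deals with the record of treatment: "The operation note from the intervention will be filed in the patient notes to allow intentional or emergency access". It states no sealing, separate filing or access log, and no instruction that the nurse works without the notes.

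The section does list other protections:
- patients are told not to disclose their treatment;
- ultrasound of the treated veins is avoided unless otherwise indicated;
- staff who collect or analyse data are absent when the envelope is opened;
- treatment decisions outside the protocol go to surgical staff who already know the allocation.

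On place and timing, the text after the AA steps under Treatment regimen says of all patients: "They will then be followed up monthly at the same site". Subsequent follow-up has the nurse assess the wound and document the BWAT at these visits.

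**The concern.** The surgeon knows the treatment, and so does the patient, since under Implementation "A member of the surgical team will then take appropriate consent from the patient for the specific procedure being carried out". Assessor blinding is therefore the main protection against detection bias. The outcome needs that protection because healing is judged by eye at a clinic visit, and the article describes no second reader or masked photograph.

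The article takes the risk seriously enough to avoid ultrasound because of it. It then places a document that identifies the arm in a record kept for the same patients, with no stated barrier. An assessor who had seen the note could call a nearly closed ulcer differently by arm, in either direction.

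The Aim section frames the question as equivalence. There, a bias that makes the arms look alike favours the conclusion the trial is set up to test, so it would not be a conservative error.

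**Working it through.** **1. The texts side by side**

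| Question | What the article states | Where |
|---|---|---|
| Who judges the wound? | The trial nurse(s), before allocation and at every follow-up visit | Personnel; Method of blinding; Subsequent follow-up |
| Are they blinded? | Yes, throughout | Method of blinding |
| Where is the treatment recorded? | Operation note, in the patient notes | Method of blinding |
| Where and when is follow-up? | Monthly, at the same site | Treatment regimen, after the AA steps |
| Does a safeguard cover the note? | None stated | Method of blinding |
| Does the nurse use the patient notes at assessment? | Not stated either way | – |

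Taking the four safeguards in turn: the first controls what the patient says, the second what a scan might show, the third who is present at envelope opening, and the fourth who makes further treatment decisions. None controls who may read the operation note. The route is open. Whether anyone takes it is not stated.

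**2. Which calls matter**

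Under Treatment regimen and Final follow-up, an ulcer called healed leaves the trial, so no later trial visit can correct a premature call. An ulcer called unhealed before 24 weeks is looked at again the next month, so a cautious early call usually does not set the primary outcome. The exposed decisions are therefore a healed call at any visit and the final call at 24 weeks.

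**3. Why no size can be given**

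The shift in one arm's healing rate would be e × b × c, where:
- e = share of that arm's deciding assessments in which the nurse knows the allocation;
- b = share of ulcers that are borderline at the deciding call;
- c = share of those borderline calls changed by the knowledge.

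None of the three is in the document. Purely as assumptions, take b = 0.10 (range 0.05 to 0.15) and c = 0.5:
- e = 1: 1 × 0.10 × 0.5 = 0.05 (0.025 to 0.075);
- e = 0.2: 0.2 × 0.10 × 0.5 = 0.01 (0.005 to 0.015);
- e = 0: no shift.

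So the answer runs from 0 to 7.5 points depending on inputs nobody has. Even b = 0.10 is generous: with 80% healing assumed under Sample size, 20% are unhealed at the end, and a borderline group of 10% would be half that size.

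**4. How sensitive the design is to a given shift**

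Inputs from Sample size: 80% healing in both arms, 15-point margin, two-sided 90% interval, 90% power.

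Reproducing the plan's figure: n per arm = 2 × 0.8 × 0.2 × (1.645 + 1.645)² / 0.15² = 153.9, rounded up to 154. This matches the stated 154 per arm.

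With SE = √(2 × 0.16 / 154) = 0.0456, equivalence power under a shift s is Φ((0.15 − s)/SE − 1.645) + Φ((0.15 + s)/SE − 1.645) − 1. For false equivalence, take a true difference of 15 points (80% v 65%) with the shift running towards no difference: 1 − Φ(1.645 − s/SE₂), where SE₂ uses 0.80 and 0.65 + s.

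| Assumed shift s | Power if arms truly equal | False equivalence if true difference is 15 points |
|---|---|---|
| 0 | 90.0% | 5.0% |
| 2 points | 86.8% | 10.7% |
| 3 points | 82.8% | 14.9% |
| 5 points | 70.5% | 26.6% |

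The table says what a shift would do if it occurred. It does not say that one will.

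**The case against.** **The unblinding step is inferred.** Trial data go on a case report form, which is kept in a locked trial cabinet and is a different record from the hospital notes. The stated purpose of filing the note is deliberate or emergency access. A reader might infer that the nurse will see the note because follow-up is at the same site, or that assessor blinding has failed. The article supports neither. This objection stands, and it limits the point to a risk.

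**Sealing and logging are operational details that an article may leave out.** This carries less weight. The section sets out its safeguards specifically and then states where the treatment record goes. The point rests on that stated arrangement, not on a missing paragraph.

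**A figure such as 5 points, a third of the margin, overstates the case.** This stands. Such a figure takes unsourced values for two inputs and assumes that the nurse saw the note in every deciding assessment.

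**Other routes are weaker than they look.** A reader might add the procedure-specific consent, but Implementation does not say where it is filed, so it matters only if it sits with the operation note. A reader might also add the principal investigator, who under Personnel is responsible for "data collection at randomisation and follow-up, and statistical analysis". No text says that this role reads operation notes, and the healing call belongs to the nurse, so this does not bear on the primary outcome as argued here.

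**Dropping ulcers with an unblinded assessor would be a post-randomisation exclusion.** This stands too. It would conflict with the intention-to-treat analysis and could add bias of its own.

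**Conclusion.** The concern holds as an unguarded risk. The article promises a blinded assessor throughout, files the record of treatment in the patient notes, and states nothing that keeps the two apart, while that assessor judges healing and scores the BWAT each month at the same site. It does not establish that any assessor has been or will be unblinded.

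The size cannot be estimated from the document, and the illustrative shifts above should not be quoted as expected bias. The conclusion rests on two modest readings: that an operation note identifies the procedure done, and that the patient notes are available at the site where follow-up takes place. The sample size is unaffected. The change is worth making because it costs almost nothing and protects the primary outcome of a trial in which only the assessor's blinding guards the healing call.

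**What to change.** Amend Method of blinding, for ulcers treated from now on, as follows:

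1. Keep the operation note, and any procedure-specific consent filed with it, in a sealed, signed envelope within the patient notes. It remains available for emergency or clinical need, and each opening is logged.
2. The trial nurse records healing status and BWAT on the case report form without the hospital notes and before the surgical team sees the patient.
3. The nurse ticks on the form whether the allocation had become known.
4. The intention-to-treat analysis remains primary. A result that leaves out ulcers whose assessor is known to have been unblinded may be reported at most as a labelled sensitivity analysis.

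The cost is an envelope and a log per patient, one tick-box, and one extra step for anyone who needs the note. Recruitment was already under way when the article was written (Trial status), so the change is prospective and does not require retrieving notes already filed.

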### Ethical approval

Ethical approval has been obtained through Galway University Hospitals Clinical Research Ethics Committee, the Research Ethics Committee governing Roscommon University Hospital. Approval was granted on 18 June 2020, ref. no. C.A. 2416, before recruitment commenced.

### Screening of patients

Patients will be recruited from Leg Ulcer Centre Ireland, a dedicated leg ulcer clinic in Roscommon University Hospital, drawing referrals from the entire Saolta Hospital Group in the West of Ireland. General practices in the area will receive written information in advance of the trial commencing to encourage direct referral to the clinic. All patients attending this clinic with a leg ulcer will be screened for eligibility including an ultrasound assessment by a member of the surgical team. Written trial information will be provided to each eligible patient, and the option to defer enrolment for a period of consideration will be offered.

### Inclusion criteria

Patients will be eligible for the trial provided that the following criteria are met:Primary or recurrent venous leg ulcerLong or short saphenous vein reflux confirmed on ultrasound assessment, defined as retrograde flow lasting for > 0.5 s in the standing positionAnkle-Brachial pressure Index (ABI) ≥ 0.8 (if ulceration prevents ABI, Toe-Brachial Index (TBI) ≥ 0.5 acceptable) or a palpable pulseUlcer size between 1 and 200 cm^2^Patient suitable for full compression bandaging

### Exclusion criteria

Patients will be excluded if any of the following apply:Pregnancy (or breastfeeding and needing to feed within 48 h of treatment).Active infection of ulcer, or infection within the last 2 weeks.Leg ulcer of non-venous aetiology as determined by clinical assessment.Isolated perforator vein reflux only.Evidence of deep venous insufficiency or thrombosis.Known hypersensitivity to Sotradecol or similar sclerosants.Previous inability to tolerate compression bandages.Presence of any contraindications for the use of compression bandages:Absence of a palpable pulse, and Ankle Brachial Index (ABI) < 0.8Decompensated congestive cardiac failure (NYHA class IV)Known hypersensitivity to any of the component materialsPatients unable to provide informed consent.Patients attending the leg ulcer clinic already will be excluded from enrolment with the same ulcer but will be eligible to enrol with a contralateral ulcer. Recurrent ipsilateral ulcers will not be excluded.

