## Administrative information

**Table Taba:** 

**Trial synopsis**	
**Title**	Axial ablation versus terminal interruption of the Reflux Source in venous ulcer management: a randomised controlled trial in venous ulcer management
**Public title**	AAVTIRS trial
**Medical condition under investigation**	Lower limb venous ulcers
**Purpose of trial**	To evaluate whether there is a clinically significant difference between axial ablation of varicose veins and peri-ulcer terminal interruption of the reflux source in promoting healing of lower limb venous ulcers.
**Primary objective**	To determine if the proportion of ulcers healed within 6 months of endovenous treatment differs between patients undergoing axial ablation of varicose veins or terminal interruption of the reflux source by peri-ulcer foam sclerotherapy.
**Secondary objectives**	To determine whether there is a significant advantage to either treatment, in a reduction in ulcer size, encouraging wound regeneration, and venous disease severity or a significant difference in patient-assessed quality of life, between the two interventions
**Trial design**	Prospective single-centre assessor-blinded randomised controlled trial
**Primary endpoint**	Proportion of ulcers healed within 6 months of intervention
**Secondary endpoints**	Absolute and relative reduction in ulcer size Time to ulcer healing BWAT score progression VCSS progression over time Change in Charing Cross Venous Ulcer Questionnaire score from treatment to completion of follow-up
**Sample size**	320 individual ulcers
**Summary of eligibility**	Patients with a leg ulcer, attributable to venous insufficiency, without any contraindication to compression or either of the comparator treatment modalities will be included.
**Screening process**	All patients with a venous ulcer attending a Leg Ulcer Centre Ireland—a dedicated venous ulcer assessment clinic in Roscommon University Hospital will be considered for enrolment.
**Randomisation**	Affected legs will be randomised in a 1:1 ratio to axial ablation or terminal interruption of the reflux source.
**Treatment**	Patients will be treated on the same day as randomisation according to their assignment to either group
**Follow-up**	Patients will be followed monthly for 6 months.
**End-of-study**	The trial will end when all patients have been enrolled and completed both treatment and 6-month follow-up.

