Endovenous management of reflux is achieved by ablation of the main superficial veins of the leg, or axial ablation (AA). If incompetent, the long or short saphenous veins, or their larger tributaries, contribute to venous ulceration by raising venous pressure, and therefore capillary hydrostatic pressure, leading to oedema, relative under-perfusion and hypoxia, and triggering an inflammatory cascade [17]. AA encourages healing by reducing venous reflux, decreasing venous pressure in distal veins, which improves the perfusion pressure at the capillary level. This improves oxygen and nutrient delivery to ulcerated areas, facilitating wound healing. Terminal interruption of the reflux source (TIRS) aims to target those veins in the distal leg which are directly responsible for transmitting the raised venous pressure to the ulcerated area and, by only treating these specific veins, achieve the necessary improvement in perfusion locally. While a review of the level 1 evidence has shown less anatomical success with ultrasound-guided foam sclerotherapy, clinical success was similar [18]. Foam sclerotherapy has been shown to be safe and effective in the management of venous ulcers [19, 20]. The ability to deliver foam via a small needle without anaesthetic makes foam sclerotherapy ideal for TIRS, and studies of perilesional sclerotherapy have found it to be safe and effective [21–23].

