#### Deferred enrolment

Patients wishing to take time to think about enrolment will be offered the chance and brought back to the clinic at an interval agreeable to them.

Patients already attending the ulcer clinic will be eligible for enrolment if they present with a new contralateral ulcer.

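### The eligibility wording does not stop a leg already randomised and treated in AAVTIRS from entering again after a recurrence, and two sections describe re-enrolment differently

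*Protocol article*

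**What the plan says.** The Exclusion criteria close with a rule for people already known to the clinic: "Patients attending the leg ulcer clinic already will be excluded from enrolment with the same ulcer but will be eligible to enrol with a contralateral" ulcer. The next sentence adds: "Recurrent ipsilateral ulcers will not be excluded". The Deferred enrolment section deals with the same group and says: "Patients already attending the ulcer clinic will be eligible for enrolment if they present with a new contralateral ulcer". It does not mention ipsilateral ulcers.

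The Inclusion criteria admit primary and recurrent ulcers alike and require long or short saphenous reflux on ultrasound. Neither list of criteria refers to a leg that has already been randomised or treated in this trial.

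On units, the Trial synopsis says "Affected legs will be randomised in a 1:1 ratio to axial ablation or terminal interruption of the reflux source" and gives the sample size as "320 individual ulcers". The Sample size section counts 308 patients.

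A participant leaves the trial at the first visit where healing is seen, or at 24 weeks. After that, "In either case subsequent treatment will be at the discretion of the surgical team" (Treatment regimen, AA). The Final follow-up section has everyone who completes follow-up seen in the ulcer clinic, so former participants can become existing clinic attenders.

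The Background describes AA as ablation of the main superficial veins. TIRS is aimed at the distal veins feeding the ulcer and is meant, "by only treating these specific veins, achieve the necessary improvement in perfusion locally".

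**The concern.** The Aim and Primary objective ask whether AA and TIRS are equivalent in healing ulcers. A leg that enters a second time has already had one of these treatments. If a former TIRS leg is then allocated to AA, its outcome follows both procedures but is counted under AA. If a former AA leg is allocated to TIRS, the reverse holds. Such entries contribute a treatment sequence to a comparison meant to be of single treatments.

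A second issue is who can come back. Saphenous reflux is needed at entry. AA is meant to remove it and TIRS leaves it alone, so a recurrent TIRS leg may qualify more readily than a recurrent AA leg. Membership of the re-entered group could then depend on the first allocation.

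The stated analyses would not deal with this. The Protocol violations section lists inability to tolerate either treatment or compression; earlier trial treatment of the same leg is not named. As written, re-entries would stay in both the intention-to-treat and the per-protocol analyses. Two recruiters reading the two eligibility sections could also apply different rules.

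**Working it through.** **Step 1: does the text allow re-entry?**
- The sentence on ipsilateral recurrence directly follows one about current clinic attenders, and its ipsilateral stands against that sentence's contralateral.
- If it meant only ulcers that recurred before the trial, it would add little, since the Inclusion criteria already admit recurrent ulcers.
- No criterion excludes a leg already randomised, and the synopsis counts ulcers.
- Re-entry is feasible in time. Recruitment began on 21 July 2020, and enrolment was to finish in the first quarter (Trial synopsis) or first half (Trial status) of 2022, a window of about 20 to 23 months.

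The text therefore permits re-entry without saying outright that a leg will be randomised twice.

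**Step 2: reproduce the stated sample size.** Inputs from the Sample size section are 80% healing in both arms, a 15-point margin, a two-sided 90% confidence interval and 90% power. For equivalence by two one-sided tests:

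n per arm = 2 × 0.8 × 0.2 × (1.645 + 1.645)² / 0.15² = 153.9, rounded up to 154, or 308 in total.

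This matches the protocol exactly. The concern does not touch that arithmetic.

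**Step 3: size of the distortion.** The protocol gives no re-entry rate and no healing rate after earlier trial treatment, so everything here is assumed. Let a share f of 308 entries be re-entered former TIRS legs, split 1:1. Let D be the healing difference among them between AA after TIRS and TIRS after TIRS. Let first entries have no true difference. Then:

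- shift in the pooled difference: d = (1 − f) × 0 + f × D = f × D
- SE = √(2 × 0.8 × 0.2 / 154) = 0.0456
- power = Φ((0.15 − d)/SE − 1.645) + Φ((0.15 + d)/SE − 1.645) − 1, which is 90.0% at d = 0

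The column for first entries only uses 154 × (1 − f) per arm with d = 0. The last column is 308 / (1 − f), rounded up.

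| f | D (points) | Re-entries | Shift (points) | Power, all entries | Power, first entries only | Entries needed for 308 first entries |
|---|---|---|---|---|---|---|
| 2% | 10 | 6 | 0.2 | 90.0% | 89.3% | 315 |
| 5% | 20 | 15 | 1.0 | 89.2% | 88.2% | 325 |
| 10% | 20 | 31 | 2.0 | 86.8% | 86.0% | 343 |
| 15% | 30 | 46 | 4.5 | 74.1% | 83.5% | 363 |

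These powers treat all entries as independent.

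**Step 4: could re-entry depend on the first allocation?** Assume equal recurrence in both arms, with saphenous reflux at recurrence in a proportion rT of TIRS legs and rA of AA legs. The former TIRS share of re-entries is rT / (rT + rA). With rT = 1.0 and rA from 0.05 to 0.50, the share runs from 95% down to 67%. With rT = 0.8 it runs from 94% to 62%. The direction follows from the mechanism in the Background; the size rests on assumed rates.

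**The case against.** The strongest reply is that the protocol never mentions re-randomising a leg. The disputed sentence concerns clinic attenders, not former participants, and can be read as keeping ulcers that recurred before the trial. The Deferred enrolment section says contralateral ulcers are eligible but does not say that only they are, so it may be incomplete rather than contradictory. This stands as far as it goes: re-entry is implied and not stated. It does not remove the gap, because nothing in the criteria prevents re-entry, and eligibility wording belongs to this document.

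A reader might infer that re-entries would be mainly former TIRS legs. The documents do not establish that. They report no reflux, recurrence or re-entry by arm. Reflux in the other saphenous vein could re-qualify an AA leg without any failure of ablation, and discretionary treatment after exit could remove reflux from a former TIRS leg.

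A reader might also infer that later entries in general compare treatment sequences, or that randomisation is compromised. Neither follows. Only re-entered legs are affected, and their second allocation is still random, so any enrichment for legs whose first treatment did not last falls on both arms.

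Finally, leaving out re-entries might seem to breach intention-to-treat. It does not: whether an entry is a re-entry is fixed before its second randomisation, and every first entry is kept as allocated.

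**Conclusion.** The point holds in a limited form. Read literally, the criteria let a leg already treated in AAVTIRS enter again, and the Exclusion criteria and Deferred enrolment sections must be reconciled. Any re-entered leg mixes a treatment sequence into the AA versus TIRS comparison, and its re-entry may depend on its first allocation.

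The number of re-entries is unknown. A leg must heal, exit and ulcerate again within the enrolment window, so they are probably few. With up to 5% re-entries and a healing difference of up to 20 points, the shift is about 1 point or less against a 15-point margin. A shift of 2 to 4.5 points appears in the scenarios with 10 to 15% re-entries and differences of 20 to 30 points. These figures assume that all re-entries are former TIRS legs and that first entries show no true difference.

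At low re-entry rates the case for change is a clean treatment contrast, not power: in the 5% scenario, power is 89.2% with all entries and 88.2% with first entries only.

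**What to change.** State the same rule in the Exclusion criteria and Deferred enrolment sections, for example: *Each leg may be randomised once. A recurrent ulcer is eligible only if that leg has not already been randomised in AAVTIRS.* Ulcers that recurred before the trial stay eligible, and so does a first ulcer on the other leg.

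If any leg has already re-entered, base the primary analysis on its first randomised entry and report all randomised entries as a sensitivity analysis.

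The wording change is one rule in two places. The price is the loss of a few entries and, if the total is not topped up, a slight loss of power: from 90.0% to 89.3% if 2% of 308 entries are lost, or to 88.2% if 5% are. Keeping 308 first entries would need 315 or 325 entries respectively.
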